### Study organization and status

Patients are selected from a population submitted to the Centro Cardiologico Monzino (CCM) as nationwide referral center for VT ablation; the SBRT treatment will be carried out at the Istituto Europeo di Oncologia (IEO) that is one of the largest radiotherapy facilities in Italy.

Recruitment started in September 2019 and is expected to end in September 2021. Two years are planned for enrollment as all participants will be selected on the basis of strict inclusion/exclusion criteria being nonresponders to, or not suitable for, any conventional approach. At the date of submission of the manuscript, 4 patients underwent SBRT and 3 completed a 3-month follow-up.

Preliminary results are expected within 1 year from the study beginning; final data analysis will be provided once follow-up period will be completed for all patients (approximately September 2022). On August 26, 2019, the STRA-MI-VT trial was prospectively registered at clinicaltrials.gov (NCT04066517).

## Discussion

STRA-MI-VT is the first Italian spontaneous, experimental, prospective, open-label study testing the role of SBRT for the treatment of recurrent VT refractory to conventional therapies, in patients with structural heart disease.

In oncology, SBRT represents a well-established treatment modality that allows to noninvasively destroy cancerous cells by delivering multiple radiation beams. In the treatment of ventricular arrhythmias, radiation therapy is supposed to modify the arrhythmogenic substrate, by eliminating the heterogeneity responsible of the reentry mechanism, similarly to RF, thus reducing the episodes of VT. Differently from RF, SBRT allows to potentially ablate deep structures, which cannot be reached by catheters [29] and to accomplish the treatment in a noninvasive, faster, and safer manner [14].

On the other side, differently from standard ablation procedures, which lead to an immediate reduction of VT events, SBRT is supposed to manifest its therapeutic effects after months [29, 37]. Indeed, in the 6–8 week period following SBRT, corresponding to the “blanking period,” VT episodes may theoretically even be facilitated, given the complex maturation process of the lesion caused by SBRT [16–18, 21]. Moreover, the precise effect of high dose of radiation for the treatment of a structurally diseased heart is not well known; an additional concern is related to the possible wrong localization of target due to respiratory and cardiac motion: this could lead to target tissue underdosing and normal tissue overdosing, undermining both efficacy and safety of the treatment.

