### Pre-discharge evaluation

After SBRT, all patients will be continuously monitored by 12-lead ECG for a period of at least 5 days; routine laboratory tests and echocardiography examination will be provided within 24 h after SBRT and before hospital discharge. Particular care will be addressed to exclude secondary effects related to SBRT.

ICD interrogation will be performed immediately after SBRT and before patient discharge to verify device and lead parameters and exclude malfunctions. As a rule, ICD ventricular arrhythmias detection and therapies will be maintained the same as before SBRT. Furthermore, ICD remote monitoring will be set up for all patients.

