### Follow-up

Adverse effects will be classified according to the international Common Terminology Criteria for Adverse Events v 5.0/CTCAE document.

A follow-up phone-call will be performed once a week for the first 4 weeks after SBRT.

Regular cardiological follow-up visits, including 12-lead ECG and ICD interrogation, will be performed 3, 6, and 12 months after SBRT. Echocardiography examination and SF-36 health questionnaire will be provided 3, 6, and 12 months after SBRT. Patients will be visited by a radiation oncologist, and thorax CT will be performed 3 and 12 months after SBRT.

Pharmacological therapy, including antiarrhythmic drugs, will be maintained the same as before SBRT during the entire follow-up.

With regard to the early post-SBRT phase and the possible occurrence of transient processes impacting on cardiac arrhythmogenicity, accordingly to literature [16–18, 21], a 6-week “blanking period,” starting immediately after SBRT treatment, will be considered in the analysis of VT recurrences during follow-up.

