### Endpoints of the study

#### Primary endpoints

Two primary endpoints of the study have been defined, represented by safety and efficacy of the treatment, respectively.Primary safety endpoint is to evaluate the safety of radiation therapy in the acute phase (during the first 30 days of the procedure) and at 3, 6, and 12 months. The incidence of serious adverse events related, or presumably related, to radioablation will be assessed as a percentage of the enrolled patients. Serious adverse events were the following:DeathCardio-circulatory arrestAcute myocardial infarctionCardiogenic shockPericarditis, myocarditis, and/or endocarditisAcute heart failureGastro-esophageal lesion (ulcer/stenosis/fistula/hemorrhage/perforation)Bronchopulmonary infectionInjury to the respiratory system (fistula/bronchial or tracheal stenosis, pulmonary fibrosis)Radio-induced oncogenesisPrimary efficacy endpoint is to evaluate the procedural effectiveness of therapy at 3, 6, and 12 months, represented by the total number of VT/VF episodes occurring after “blanking period,” compared with the period preceding the radioablation procedure (6 months).

VT episodes will be categorized as follows:VT episode > 30 s, regardless of the intervention of the ICDVT episode conditioning ICD intervention by means of “anti-tachycardia pacing” electrical therapy (without shock delivery)VT episode conditioning ICD shock intervention

The 6-week “blanking period” will start on the procedure day.

As a rule, pharmacological therapy, including antiarrhythmic drugs, will be maintained the same as before SBRT during the follow-up period. Changes of the pharmacological therapy will be determined only by specific clinical reasons.

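### VT/VF in the first 6 weeks after SBRT is left out of the efficacy count and is not a listed safety event unless a listed outcome follows; ICD or lead malfunction is not listed either

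*Protocol article*

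**What the plan says.** **Efficacy.** Under Primary endpoints, efficacy is "represented by the total number of VT/VF episodes occurring after" the blanking period, read at 3, 6 and 12 months and "compared with the period preceding the radioablation procedure (6 months"). The same section fixes the window: "The 6-week “blanking period” will start on the procedure day". The Follow-up section attributes the blanking to possible transient effects on arrhythmogenicity and says that it "will be considered in the analysis of VT recurrences during follow-up".

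**Why early VT is set aside.** The Discussion states that in the weeks after treatment "VT episodes may theoretically even be facilitated, given the complex maturation process of the lesion caused by SBRT". It gives this phase as 6 to 8 weeks and equates it with the blanking period, whereas Follow-up and Primary endpoints fix 6 weeks.

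**Safety.** The primary safety measure is the percentage of enrolled patients with serious adverse events that are related, or presumed related, to SBRT. The events are introduced by "Serious adverse events were the following", and ten items follow: death, arrest, myocardial infarction, cardiogenic shock, inflammation of the pericardium, myocardium or endocardium, acute heart failure, gastro-esophageal lesions, bronchopulmonary infection, respiratory injury and radiation-induced cancer.

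**The device.** Every participant has an ICD (Eligibility criteria). The Treatment section contours it as an organ at risk, the Discussion names possible damage to it, and Pre-discharge evaluation has it interrogated "to verify device and lead parameters and exclude malfunctions".

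**The concern.** The reason given for leaving early episodes out of efficacy is that the treatment may provoke them. That is a sound reason not to score them as treatment failure, and equally a reason to count them as possible harm. The safety list does not pick up what the blanking removes. Sustained VT, VT treated by pacing or shock, or an electrical storm in the first 6 weeks therefore belongs to neither primary endpoint if no listed outcome follows.

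ICD or lead malfunction is a separate gap of the same kind: a recognised and checked hazard that has no place in the primary safety rate.

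At stake is the claim that the trial is built to test, that SBRT reduces VT burden safely and effectively. The two primary results could support that claim for patients whose VT worsened in the weeks after treatment, or whose device was damaged.

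**Working it through.** **1. Where each event counts**

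| Event in days 0 to 42 | Efficacy | Primary safety list | 30-day stopping rule | Secondary endpoints |
|---|---|---|---|---|
| VT/VF leading to death | no | yes, if related | yes | mortality |
| VT/VF leading to arrest or cardiogenic shock | no | yes, if related | yes | no |
| VT/VF leading to acute heart failure | no | yes, if related | no | no |
| Storm, incessant VT, or VT treated by pacing or shock, without those outcomes | no | no | no | no |
| ICD or lead malfunction | no | no | no | no |

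The stopping rule names death, myocardial infarction, cardiogenic shock and arrest. The secondary endpoints are mortality, quality of life and ejection fraction. An event may influence quality of life or ejection fraction, but it is not counted there as such. The 30-day acute safety phase lies wholly inside the 42 blanked days.

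**2. Share of follow-up that is blanked**

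- 3 months: 42 / 91.3 = 46%
- 6 months: 42 / 182.6 = 23%
- 12 months: 42 / 365.25 = 11.5%

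**3. Illustration of what could go unseen**

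The plan gives no figure for early VT, so there is none to reproduce. The sample-size paragraph supplies a baseline of 10 episodes in 3 months and a 60% reduction. Assumption, not in the document: the rate is multiplied by *m* during blanking and then falls by 60%.

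- Expected in the blanked window at the baseline rate: 10 × 42 / 91.3 = 4.60
- Expected in the rest of the 3 months at the baseline rate: 10 − 4.60 = 5.40; after a 60% reduction, 0.4 × 5.40 = 2.16
- Total over 3 months = 4.60 × *m* + 2.16

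| *m* | Total, against 10 before | Net change over 3 months | Change in post-blanking rate |
|---|---|---|---|
| 1 | 6.8 | −32% | −60% |
| 1.5 | 9.1 | −9% | −60% |
| 2 | 11.4 | +14% | −60% |
| 3 | 16.0 | +60% | −60% |

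Break-even: *m* = (10 − 2.16) / 4.60 = 1.7. The effect dilutes with time. At *m* = 2 the net reduction counted from day 0 is 23% at 6 months and 42% at 12 months; at *m* = 3 it is about 0% and 30%.

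**4. Why not simply add any ICD-treated VT to the safety list**

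With no SBRT effect at all, about 4.6 episodes are expected in 42 days. If these were Poisson (assumption) and all ICD-treated, the share of patients with at least one would be 1 − e^(−4.6) = 99%. A percentage-of-patients endpoint would be saturated and uninformative.

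**The case against.** Several points on the other side stand.

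- **Blanking is legitimate.** It is explained and referenced, and it is not an error in the efficacy analysis.
- **Early VT is also the disease.** Patients enter with at least three ICD-treated episodes or incessant VT, so leaving ordinary recurrences out of a list of treatment-related events is defensible. This limits the remedy to new or worsened arrhythmia and to a comparison with the patient's own earlier rate.
- **The events are monitored.** There are at least 5 days of continuous ECG, device interrogation after treatment and before discharge, remote monitoring for all, weekly calls for 4 weeks and CTCAE classification. Early VT and device faults would probably be recorded. Recording them does not put them in a primary endpoint.
- **A day-0 sensitivity analysis is usually left to the analysis plan.** Its absence from the article is not a fault. It is offered only as part of the repair.

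A reader might also infer more than the documents support:

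- *That no VT in the first 30 days can ever count.* It counts through death, arrest, cardiogenic shock or acute heart failure judged related, and all of these except acute heart failure also feed the stopping rule.
- *That the protocol expects proarrhythmia, or that this is the main foreseeable harm.* The Discussion calls it theoretical. The SBRT complications that it reports from an earlier trial are heart failure exacerbation and pericarditis, both of which are covered by the list.
- *That nearly half of follow-up is discarded.* The 46% applies only to the 3-month reading.

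**Conclusion.** The concern holds as a gap between two endpoint definitions. VT/VF in days 0 to 42 that does not lead to death, arrest, cardiogenic shock or related acute heart failure counts in neither primary endpoint, and ICD or lead malfunction at any time is not a listed safety event. This follows from the text and needs no assumption beyond reading the ten-item list as complete, which is how it is introduced.

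The gap matters most at the 3-month reading (46% of the window) and least at 12 months (11.5%). The 1.7-fold break-even is an illustration; the documents give no estimate of how far, if at all, the early VT rate rises. The sample size of 15 plays no part. The point should be repaired, but it does not invalidate the design.

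**What to change.** 1. Keep the 6-week blanking for the primary efficacy analysis, and reconcile the 6 weeks in the endpoint definition with the 6 to 8 weeks in the Discussion.
2. Add two items to the listed safety events: electrical storm or incessant VT that is new or worse than the patient's own pre-SBRT state, with the terms defined; and ICD or lead malfunction after SBRT.
3. Report VT/VF episodes and ICD shocks in days 0 to 42 per patient as a named safety outcome, as a rate against the patient's own pre-SBRT rate. Do not add any ICD-treated VT to the percentage-of-patients composite.
4. Repeat the paired efficacy comparison counting from day 0 as a pre-specified sensitivity analysis.

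**Cost.** No new data, visits or patients: ICD interrogation, remote monitoring and adverse-effect evaluation already supply the information. It does require a protocol amendment to a registered, open-label trial with recruitment open and 4 patients treated when the article was submitted. The amendment should state how those 4 are handled. The reported safety rate may become less favourable.

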### Analysis of previous experiences

To the best of our knowledge, nine clinical studies are currently underway regarding the use of stereotactic radiation therapy for the treatment of ventricular arrhythmias, registered at clinicaltrials.gov as NCT02919618, NCT02661048, NCT03601832, NCT03819504, NCT03349892 (suspended), NCT04066517, NCT04162171, NCT04065802, and NCT03867747. Results are available and published exclusively for the first two of them.

Some studies in literature already showed that radioablation allows to reduce the occurrence of arrhythmic episodes without significant side effects directly imputable to the treatment and hence demonstrated both its efficacy and safety. Loo and colleagues [20] carried out the first-in-human treatment of ventricular arrhythmia. No acute and late complications were reported, but the efficacy of the treatment was limited to the first months of the treatment. Efficacy and short-term safety were also confirmed in other studies in which only one patient was treated [22, 23, 26–28, 30]. Neuwirth and colleagues [24] reported the second largest case series on the safety and efficacy of SBRT to treat patients with recurrent VT. During 3 months after SBRT, VT burden was reduced by 87.5% and the treatment was well-tolerated; out of the 10 treated patients, only 4 reported nauseas and only 1 presented gradual progression of mitral valve regurgitation. Severe short-term complications were instead observed by Robinson and colleagues [13], in the context of the abovementioned ENCORE-VT trial. As a matter of fact, out of the 19 enrolled patients, VT episodes were reduced in almost all patients with consequent improvement in quality of life, but 2 patients experienced transient heart failure exacerbation and pericarditis, most likely caused by SBRT. Last but not least, in a series of 5 high-risk patients with scar-related VT, the safety profile of SBRT was confirmed to be favorable by Gianni and colleagues [38]; despite good initial results, all patients experienced however clinically significant recurrences over the mid- to late-term. Given these in part contradictory evidences about long-term efficacy and safety, and due to the fact that SBRT has been mainly used as a palliative therapy in patients with short life expectancy, further studies in the field are eventually required.

In nearly all the investigations, prescription dose was 25 Gy delivered in a single fraction, even though preclinical studies demonstrated the safety of more escalated treatments [12]. Scholz and colleagues [28] prescribed a single dose of 24 Gy to the PTV-encompassing 80% isodose. Zeng and colleagues [29] opted for an even more cautious approach (24 Gy in 3 fractions), justified by the fact that VT was secondary to a cardiac tumor and that the tissue to ablate was in a close anatomical relationship to the left anterior descending artery. Actually, one major issue is to evaluate the optimal dose to deliver to the heart, which should be effective but safe at the same time, minimizing induced toxicity to surrounding tissues and possible damages to the ICD [39, 40]. Data available from literature are not enough to define the best dosimetric variables as, in oncological applications, the heart is rarely the target organ, being intracardiac malignancies quite uncommon. On the contrary, the heart often represents one of the OARs with the highest avoidance priority when irradiating thoracic tumors. Cardiac and particularly respiratory-induced thoracic motion represent an additional level of complexity, as the treatment system must be able to accurately track the moving target [37]. According to this protocol, this problem is overcome by defining a cardiac and respiratory ITV, which considers both causes of motion [37].

### Possible effects of SBRT: Addressing “pros” and “cons”

The benefit supposed to derive from the use of SBRT is represented by the superior efficacy in the control of VT with respect to the conventional percutaneous procedure. This superior efficacy specifically derives from the hypothesis that the SBRT can result in a more appropriate and discrete substrate modification in patients in whom the conventional approach has failed. In a clinical setting, SBRT will be offered as an option in patients who are not eligible to any interventional or surgical approach due to an unacceptably high procedural risk.

Theoretical disadvantages associated with SBRT relate to the fact that we will use a novel therapeutic approach that has been tested only in selected groups of patients; therefore, there is no evidence of its efficacy as a standard treatment. Of note, for STRA-MI-VT patients, this limitation has little significance as all participants will be first categorized as nonresponders or not suitable for any conventional approach. In addition, SBRT may be responsible for cardiac and noncardiac adverse effects, due to the higher radiation exposure of the patients. Even if these effects are, based on the literature, transient, and of mild to moderate entity, specific attention will be given in our study to prospectively evaluate cost-effectiveness of SBRT.

## Conclusions

The existing research confirms that SBRT might represent a relatively effective and well-tolerated therapeutic option in patients with VT who have failed other approaches [37].

STRA-MI-VT study aims at demonstrating that SBRT may represent an alternative therapeutic option in selected patients with substrate-related VT, thanks to a potentially favorable cost-effectiveness ratio. An advanced combined multimodal imaging will be used to characterize the arrhythmogenic substrate and to identify the target for SBRT, thus STRA-MI-VT is supposed to provide significant information to define the adequacy of this novel imaging-integration methodology.

SBRT is widely used in oncology to treat small primary or secondary malignant lesions to high doses in few fractions, leading to local control of about 90% [41]. In the last years, it has been proposed to some benign conditions like trigeminal neuropathy, acoustic neurinomas, or arteriovenous malformations [42]. VT is a condition that might prospectively benefit from this noninvasive approach.

Preliminary results are expected to be available within 1 year. If primary endpoints of STRA-MI-VT will be reached, SBRT has the potential to be offered as a novel therapeutic option to a larger population of patients with mostly intractable VTs, based on the attractive possibility to treat also substrates inaccessible to conventional approaches in a safe and less-invasive manner.

Finally, the methodology of the STRA-MI-VT is based on the cooperation of different teams, with specific competences in arrhythmology, cardiac imaging, and radiation therapy, in an attempt to validate and share a multidisciplinary workflow process that may represent the premise for future clinical experiences in the field.

## Data Availability

Not appropriate.
